#### Sample size/feasibility

The mean NICU LOS over the last 10 years has consistently been 15 days (reported above) so it was selected as a conservative counterfactual and standard deviation (SD) was set at 3 days based on local and national data to provide adequate power to detect small differences in LOS. Intra-cluster correlation (ICC) was conservatively estimated at 0.1. With 8 sites, 8 initiation steps, and 1 site initiated per step (Fig. 2) over the course of 3 years, a mean LOS of 15 days (SD 3 days), and an ICC of 0.1, the study will have at least 80% power with a two-sided 5% significance level to detect a 19% difference (2.75 days) in NICU LOS.

There were 4.35 cases per 1,000 live births in 2018/2019 and approximately 56,000 livebirths in Alberta in 2018, thus an estimated 244 affected newborns are born per year. Given the rate of rise of NAS cases over the last decade it is likely that approximately 300 infants will be diagnosed with NAS yearly by 2023. Given that 75% of infants with NAS are currently admitted to NICU in Alberta, this corresponds to 225 patients being admitted to NICU by 2023.

Approximately 169 patients/year will be eligible for inclusion in the study (75% of the estimated 225 patients/year) [42]. We estimate that 4 to 6 mother-infant dyads would participate at each implementation site in each 3-month study period. Based on the 70% maternal participation rate of the MMUNA program it is estimated that approximately 20–30 mother-infant dyads would participate in a rooming-in model of care in Year 1, 90 in Year 2, and an increase to 120 dyads/year by the end of year 3, for a total of 240 expected participating dyads during the NASCENT study. 75% of participating dyads in the rooming-in model of care are expected to take part in the research (*i.e*., secondary health outcomes and 6 months follow up) considering the population involved.

### Mother-Infant dyad outcomes analysis

#### Statistical Analysis

NICU LOS was chosen as the primary outcome because NICU admission may occur for several medical reasons unrelated to NAS and a difference in LOS may be more meaningful in understanding NAS severity. Cases with no NICU admission will be assigned a NICU LOS of 0 days. Generalized Linear Mixed Models and Estimating Equations will be used in analyzing the primary and secondary outcomes: rates of pharmacological management of NAS, child apprehension, maternal participation in an ODP, maternal mental health, parenting self-efficacy, quality of life at discharge at 6 months follow up and, babies’ developmental outcomes at 6 months follow-up (see aim 1 above).

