**Discussion:**

The primary expected outcome is reduced NICU LOS. Secondary expected outcomes include decreased rates of pharmacological management of NAS and child apprehension, increased maternal ODP participation, and improved 6-month outcomes for mothers and infants. Moreover, the NASCENT program will generate the detailed, multi-site evidence needed to accelerate the uptake, scale, and spread of this evidence-based intervention throughout Alberta, leading to more appropriate and effective care and use of healthcare resources.

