### Aim 1: Assess the impact of the rooming-in model of care intervention

#### Aim 1: design

A Stepped Wedge Cluster Randomized Controlled Trial (SW-cRCT) will be conducted with 8 participating sites in Alberta over the course of the study. The SW-cRCT is ideally suited to interventions that require implementation by multiple sites with impact on workflow and the structure of care delivery [55]. This design includes randomized sequential roll out of the intervention to all sites over time. Baseline data acts as the pre-intervention control comparisons and secular trends can be accounted for due to concurrent control groups for most periods. The analysis can also assess whether the impact of the intervention changes over time.

We intend to introduce NASCENT at a new hospital every 3 months following a minimum of 6 months of initial baseline data collection as illustrated in Fig. 2. Hospitals will implement the intervention following a computer-generated stratified random allocation sequence created by the independent study statistician. Stratification based on ‘readiness’ will be used to allow the two sites with existing rooming-in programs and experience to implement early in the study to inform care at sites implementing subsequently.

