**Fig. 2 Fig2:**
[figure not shown]
The NASCENT stepped wedge cluster design. Launch phase: baseline anonymous data collection (continues through all phases). Pre-implementation phase: formative readiness evaluation and development of tailored interventions. Implementation phase: targeted interventions, participant data collection, formative evaluation. Post implementation: formative evaluation and 6-month health and social assessment

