### Data collection and management

Prospective data collection will be developed in consultation with experts from existing NAS programs and informed by the Minimum Dataset for NAS registry recommendations [56]. Anonymous LOS data will be collected from administrative data for NAS admissions at all sites pre-initiation and at each implementation phase for patients that are not consenting participants in the study. Standardized forms will be used to collect data, including LOS, for consenting participants at discharge and at 6 months follow-up (Table 1 ).

**Table 1 Tab1:** Data collection: rooming-in intervention economic evaluation, and short-term social, health, and developmental outcomes

All sites	Number of Mother &Infant Dyads	Months Collected	Data
**Baseline data** (Anonymous) Throughout all phases	160–240	6 – 27	LOS in NICU, pharmacological management, breastfeeding at discharge and apprehension rates
**During implementation-** (consenting participants at/before discharge)	Up to 240	9 – 30	LOS, Perinatal characteristics, NAS pharmacologic management, rates of breastfeeding, maternal participation in ODP/VODP, child apprehension
**After discharge** (consenting participants at 6 months)	Up to 240	24	Maternal: participation in ODP/VODP, breastfeeding duration, involvement with Children’s Services, maternal depression (Edinburgh), parenting self-efficacy, quality of life Baby: NAS pharmacologic management, short-term developmental assessment using the Ages and Stages Questionnaire: SE-2 and ASQ 3

De-identified data will be collected and managed using REDCap electronic data capture tools hosted at The University of Alberta [57, 58]. REDCap (Research Electronic Data Capture) is a secure, web-based software platform designed to support data capture for research studies. In addition to chart review, provincial and national health related databases will be used to collect baseline LOS, perinatal characteristics, and data to inform the economic analysis. Data linkage will be through unique identifiers and probabilistic linkage. Data collection will be coordinated by site champions and the NASCENT study investigators. Confidentiality will be maintained throughout the study. Only study investigators will have access to the final dataset.

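### The 6-month questionnaire outcomes, and ODP participation as its collection is described, have no control-phase data, so the trial cannot compare them with standard care

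*Protocol article*

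**What the plan says.** All places are in the Protocol article.

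- **Analysis.** The Statistical Analysis section states that "Generalized Linear Mixed Models and Estimating Equations will be used in analyzing the primary and secondary outcomes". The secondary list includes "maternal participation in an ODP, maternal mental health, parenting self-efficacy, quality of life at discharge at 6 months follow up", followed by infant developmental outcomes at 6 months. No distinction is made between outcomes to be compared with standard care and outcomes to be described.
- **Intent.** The Abstract's Discussion paragraph expects "increased maternal ODP participation, and improved 6-month outcomes for mothers and infants". The Abstract's Methods paragraph says baseline data will be compared with post-implementation data. Aim 1 frames the secondary objective as change in maternal and infant health and social outcomes.
- **Comparator.** Aim 1: design says "Baseline data acts as the pre-intervention control comparisons".
- **Data in the comparator.** The anonymous baseline row of Table 1 contains "LOS in NICU, pharmacological management, breastfeeding at discharge and apprehension rates".
- **Data from participants.** The implementation row, for consenting participants at or before discharge, contains "LOS, Perinatal characteristics, NAS pharmacologic management, rates of breastfeeding, maternal participation in ODP/VODP, child apprehension". Depression, self-efficacy, quality of life and the infant developmental questionnaires appear only in the row for "consenting participants at 6 months".
- **Timing.** The Fig. 2 legend makes the launch-phase data anonymous and places participant data later: "Implementation phase: targeted interventions, participant data collection, formative evaluation".

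**The concern.** A stepped-wedge trial estimates an effect by comparing site-periods before crossover with site-periods after it. An outcome measured only after crossover has nothing on the other side of that comparison. The protocol nevertheless puts several such outcomes in the same analysis sentence as the primary outcome and states a direction for them.

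The risk is in the eventual report. A statement that the programme raised ODP uptake, or improved maternal mood, parenting confidence, quality of life or infant development, would rest on uncontrolled data from mothers who agreed both to room in and to be followed up. The Economic analysis section adds to this: it plans to compare costs and outcomes with baseline care, and says the 6-month follow-up will inform that work.

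**Working it through.** **1. Reproduce the collection windows in Table 1.** Inputs: at least 6 months of baseline and one new hospital every 3 months (Aim 1: design); 8 sites and 3 years, i.e. 36 months (Sample size/feasibility).

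- Control time: 6 months at the first site; 6 + 7 × 3 = 27 months at the last. Table 1's baseline row gives 6 to 27.
- Time after crossover: 36 − 27 = 9 months at the last site; 36 − 6 = 30 months at the first. Table 1's consenting-participant row gives 9 to 30.

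Both windows are reproduced. Read this way, the consenting rows cover time after crossover only. Two other places agree. The target population section evaluates dyads admitted to rooming-in, and the sample size section draws the secondary and 6-month outcomes from 75% of rooming-in dyads.

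**2. Set outcomes against sources (Table 1).**

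| Outcome | Anonymous, all phases | Consenting, by discharge | Consenting, 6 months |
|---|---|---|---|
| NICU length of stay | yes | yes (as LOS) | no |
| Pharmacological management | yes | yes | yes |
| Breastfeeding | yes (at discharge) | yes | yes (duration) |
| Child apprehension | yes | yes | Children's Services involvement |
| ODP participation | no | yes | yes |
| Maternal depression | no | no | yes |
| Parenting self-efficacy | no | no | yes |
| Quality of life | no | no | yes |
| Infant development | no | no | yes |

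Control observations for the last five rows: 0. Intervention-phase observations: up to 240 by Table 1, or about 0.75 × 240 = 180 by the sample size section.

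The two sites with existing rooming-in do not fill the gap, because their baseline data are also anonymous and hold the same four items.

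**3. Check whether an effect can be identified.** Take the usual stepped-wedge form (an assumption, since the article does not write out the model): link(mean) = period effect + θ × intervention indicator + random site effect. Use 3-month periods and one site crossing over per period. With 12 periods (36 months, 2 of them baseline), the site-periods after crossover number 10 + 9 + … + 3 = 52 of 96.

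| Layout | Site-periods observed | Columns | Rank |
|---|---|---|---|
| 9 periods, after crossover only | 36 of 72 | 9 | 8 |
| 10 periods, after crossover only | 36 of 80 | 9 | 8 |
| 12 periods, after crossover only | 52 of 96 | 11 | 10 |
| 12 periods, both phases | 96 of 96 | 13 | 13 |

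When only post-crossover cells are observed, the indicator is 1 in every row and equals the sum of the period columns, so θ has no unique value. Dropping the period effects does not help: intercept plus indicator has rank 1 of 2. The number of dyads per cell does not enter the calculation. Measuring in both phases restores full rank.

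**4. What remains estimable.** Intervention-phase levels, the change in ODP participation from discharge to 6 months, and trends with time since implementation. None of these is a contrast with standard care.

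**The case against.** **The model is not written down.** The article names methods, not an indicator or a contrast for each secondary outcome, and mixed models or estimating equations also suit site-clustered and repeated data. This stands in part. A reader might infer that nothing at all can be estimated, or that these methods must be struck out for these outcomes. The documents do not support that: descriptive estimates remain possible and need an allowance for clustering. What fails is the comparison with standard care, which Aim 1 and the Abstract do express.

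**ODP participation might come from elsewhere.** The data section adds chart review and provincial and national databases. It names these for baseline length of stay, perinatal characteristics and economic inputs, not for ODP participation, but it does not rule ODP out. A reader might therefore go too far in saying that ODP control data definitely will not exist. The supportable statement is that no control source is given. The argument carries little weight for the questionnaire scales, which Table 1 ties to the 6-month follow-up of consenting participants.

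**This is a condensed article, and expected outcomes are hypotheses.** Both are fair cautions. But Table 1 states who supplies which variable, and a later analysis plan cannot analyse control data that were not collected. A hypothesis is harmless until the trial is presented as able to test it.

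**A selection figure.** A reader might multiply the 70% participation rate by the 75% research uptake to size the problem. The 70% comes from another programme, its denominator is not defined, and the product would describe selection rather than the missing comparator. It is not a measure of this defect.

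**Conclusion.** The stated data sources and the stated analysis conflict. Four secondary outcome groups (maternal mental health, parenting self-efficacy, quality of life and infant development at 6 months) have no control observations, so their stepped-wedge effect cannot be estimated at any sample size. ODP participation is in the same position as collection is described, with less certainty because another source could be arranged.

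The conclusion assumes that Table 1 describes collection correctly and that consenting-participant data begin at crossover, which the reproduced windows and the Fig. 2 legend support.

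A reader might infer that the trial's main result, or all its secondary comparisons, are compromised. They are not. NICU length of stay and its power statement are untouched, and pharmacological management, child apprehension and breastfeeding at discharge are collected in both phases. The point should be fixed, but it does not threaten the trial.

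**What to change.** 1. **Six-month questionnaire outcomes.** In the Abstract, the Aim 1 objectives and the Statistical Analysis section, label maternal mental health, parenting self-efficacy, quality of life and infant development as descriptive and non-comparative. Report intervention-phase estimates with 95% confidence intervals that allow for site clustering. Mixed models or estimating equations may be kept for this. Make no claim of improvement over standard care.
2. **ODP participation.** Either extract it from chart review or administrative data for mothers in both control and intervention periods, state that source in Table 1, and keep it comparative; or label it descriptive as well.
3. **Comparative secondary outcomes.** Limit these to outcomes collected in both phases: pharmacological management, child apprehension and breastfeeding at discharge. Add breastfeeding to the Statistical Analysis list, where it is currently absent although Table 1 collects it throughout.

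Possible wording for the Statistical Analysis section:

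> Pharmacological management, child apprehension and breastfeeding at discharge will be compared between control and intervention periods. Outcomes measured only in consenting participants after implementation will be summarised with 95% confidence intervals allowing for clustering by site, without comparison to standard care.

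**Cost.** Items 1 and 3 are wording changes, and the downside is fewer causal claims. Keeping ODP comparative adds data extraction in control periods. The trial status is not yet recruiting, so this can still be arranged before any site crosses over.

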#### Economic analysis

Data extracted for the economic analysis will be used to calculate the cost avoidance related to shifting newborn care from the NICU to post-partum/pediatric units. We will compare both costs and outcomes of the NASCENT intervention with the baseline standard of care, calculating the decrease in overall NICU bed use and LOS. A significant proportion of the expected cost savings arising from this intervention do not relate to direct health system resources but include broader societal costs related to involvement with Children’s Services and decreased rates of child apprehension. These societal cost-savings will be determined using data collected from the Canadian Institute for Health Information and administrative databases. The 6 months post-discharge mother-infant dyad follow up will help ascertain short-term mother and infant health and infant developmental outcomes and will inform our economic analysis. It is also recognized that children and adolescents in care have poorer educational outcomes, higher hospitalization rates, and greater risk of attempting or committing suicide than those not in care [59–61]. These longer-term outcomes are outside the scope of NASCENT, but it is anticipated that maintaining and supporting the mother-infant dyad will have long-reaching positive impacts. A complete economic analysis and final statistical analysis for the entire study will not be performed until completion of the study.

### Aim 2: Implement the rooming-in intervention across Alberta

#### Aim 2 design

The Alberta NASCENT study is designed to assist teams in shifting from a medicalized model of care (NICU and pharmaceuticals) to a rooming-in model of care across Alberta. The overall goal is to support instigating or enhancing practice, care, and culture change through *Capacity Building* (Table 2) in each site, so it becomes the new normal practice. Capacity building is contextually driven, and measures will be taken to identify what the drivers are.

**Table 2 Tab2:** Capacity Building Elements

Team and leadership	*Forming the implementation team; building a strong effective care team; establishing commitment; motivation, joint goals, responsibility, success; developing attentive leadership at units and with site champions*
Knowledge	*Founding expertise; acquiring contextual knowledge (e.g., addictions and mental health); advancing individual competencies (care providers, families/ mothers); adopting evidence-based practice and care (e.g., ESC, mother & baby-/ family- centered, trauma-informed, culturally safe care)*
Ability to change	*Changing norms of traditional care; reflecting on attitudes and beliefs; forming a unit climate supportive of learning, reflection, and evaluation*
Relationships	*Working towards trusting relationships with mothers and families; building connections within the hospital and across sectors; fostering linkages of acute care and community settings who provide care to mothers to support women pre- and post-delivery, to ensure continuum of care; ensuring open on-going channels of communication among implementation team, staff, patients, and administration*

#### Formative evaluation

Formative evaluation with care teams involved in infant care for NAS will be conducted throughout all implementation phases and will guide the development of tailored strategies to support effective implementation and bring about provider and unit-level practice change. Throughout the implementation process (launch phase, pre- during- and post-implementation), and in partnership with each unit, we will identify: site-specific facilitators and barriers, contextual influences on experiences of care teams’ interactions with women with substance use disorders and babies with NAS, satisfaction of implementation team members and participants, evaluation of interventions, and lessons learned within and across sites to articulate unique contextual needs, and potential interventions to support sustainability. Elements contributing to sustainability and retention of the rooming-in model of care including transitions to and from the hospital to community, leaders and champions, and support provided by administration will also be explored. Using theory-based surveys, interviews, and focus groups informed by CFIR [47], the COM-B Framework, and the Behaviour Change Wheel [48] we will seek to understand the implementation process and outcomes through exploration of attitudes, perspectives, and experiences to guide and attain practice and culture behaviour change (Table 3).

**Table 3 Tab3:** Behaviour Change Components for NASCENT

**Practice change** Individuals, units, and hospitals	*- Establish referral processes* *- Admit NAS babies to rooming-in program instead of NICU* - *Use ESC or other methods to minimize the use of pharmacological interventions* - *Provide care for NAS babies and support mothers for longer period in hospital than usually provided for delivering mothers* - *Support mothers and families in breastfeeding and caring for the baby while in hospital* - *Ensure supports are in place in the community upon discharge*
**Culture change** Individuals	- *Health care providers provide trauma-informed care reflected as behaviours that support women to take care of their babies: e.g., listening, encouraging mothers, providing care with respect and compassion* - *Individuals’ behaviours that are NOT based on stigma and bias* - *Providing care that demonstrates cultural safety* - *Optimal care, equity based for perinatal women using substances* - *Health care providers provide hopeful care (supporting the patient’s goals and capacity to achieve their goals, and care providers’ belief in the possibility of the patient living their desired future)*

Ongoing findings will be shared with stakeholders and inform the development of tailored and strategic interventions targeting barriers and leveraging existing facilitators to improve the operation, management, and sustainability of the rooming-in model of care and enhance community involvement. Part of the planned intervention is to access existing resources to assist health care providers in examining their behaviours and identifying unconscious bias. This will help identify the elements, mechanisms, tools, and strategies to optimize the NAS rooming-in approach success (*i.e.*, uptake, sustainability, and scale of the rooming-in model of care within the unique context of sites). The NASCENT intervention plan is ideally suited to understanding and changing hospital culture and individual staff behaviour related to NAS care.

